### **VentFirst Arm**

- At 30 seconds, the neonatology provider will give CPAP if the infant is breathing well or PPV if not. Ventilatory assistance will continue from 30 seconds until the script reader announces “120 seconds, clamp cord”.
- If, during the intervention, an infant getting CPAP stops breathing, PPV will start. Conversely, if an infant is getting PPV and starts breathing, CPAP will be given.
- For infants in the VentFirst arm, per NRP guidelines, heart rate will be assessed after CPAP or PPV are initiated. This will be done either by brief gentle cord palpation or with a heart rate monitor if available. HR will be assessed at 60 and 90 seconds. If at either time the HR is <100 beats/minute, standard NRP steps will be done to improve ventilation and HR. This includes repositioning the mask, suctioning the mouth/nose, opening the mouth slightly, or increasing the pressure of the PPV breaths. If HR is persistently low, at the discretion of the OB and Neonatal providers the cord may be clamped prior to 120 seconds.

**NOTE:** Settings for ventilatory assistance for both groups will be based on standard NRP guidelines and each hospital’s protocols, with FiO2 30%, PEEP 5-6 cm H2O, Peak Inspiratory Pressure 20 cm H2O (with option to increase if the heart rate is low or PPV is judged to be inadequate).

### **Post-Delivery Instructions and Data Collection (both arms)**

#### **Infant (neonatology team):**

- Number of seconds after birth that the cord was actually clamped is recorded by the VFF. For quality control purposes, audio recording of the DR intervention may be performed for later review by the site CRC or PI to validate data written on DR script.
- If the cord was clamped more than +/- 15 seconds from the target time required in the specific study arm (30-60, or 120 sec), the VFF will record a reason on the delivery data sheet and a protocol deviation will be reported (see section 10.2.2).
- After the baby is moved to the resuscitation table, further resuscitation measures are carried out per NRP guidelines.

#### **Mother (OB team):**

- If oxytocin is given to the mother after delivery, the guideline will be to give after cord clamping as noted below.
- Umbilical cord arterial and venous blood gases will be requested per routine care after the cord is cut.
- If the mother has acute post-partum hemorrhage ( $\geq 1000$  ml estimated blood loss within 24 hours of delivery), this will be noted as an SAE as described below and in the MOP. If the mother has a retained placenta, this will also be recorded in the database and reported as an AE. Post-partum delivery-related infection prior to the mother's hospital discharge will also be recorded and reported as an AE. These data will be sought in the mother's medical record.

**NOTE: In case of an unanticipated emergency, the Obstetrician or Neonatologist may terminate or deviate from the protocol.**

### **Prohibited and Concomitant Medications**

All medications, interventions, procedures and blood products normally provided as part of routine care are permitted in this study. Data collected for the purposes of the study will be limited to the administration of the specific medications or blood products listed below. This data will be entered into the CRF's by the CRC based on review of the mother's and infant's medical records.

**Data collected on maternal medications prior to and after delivery:**

- Number of prenatal steroid doses
- Magnesium given within 24 hours prior to delivery
- Oxytocin given after delivery (and timing related to cord clamping)

**NOTE:** It will be recommended that if oxytocin is given to the mother during the third stage of labor (after delivery of the infant and before delivery of the placenta) *it should be given after the cord is clamped.*

**Data collected on infant medications:**

- Number of surfactant doses from birth to 10 days
- Volume boluses during the first 24 hours after birth
- Medications for low blood pressure during the first 24 hours after birth
- Indomethacin given in the first 2 days after birth for IVH prevention
- Medication given after day 2 to treat a patent ductus arteriosus
- Total number of red blood cell transfusions given from birth to 10 days

**Duration of Study Participation**

The study intervention will take place in the first 2 minutes after birth.

Follow-up will be done from birth to 36 weeks PMA or until hospital discharge (whichever comes first) and then again at 18 to 24 months corrected gestational age (CGA). The 18 – 24 month follow-up will involve a Neurodevelopmental clinic visit done for routine care.

**Discontinuation/Withdrawal from Study**

Participants may be withdrawn or be discontinued from the study at any time for any of the following reasons:

- Mother withdraws consent
- Obstetrician or neonatology physician determines that a maternal or fetal condition precludes the study intervention
- Sponsor PI closes the study
- The DSMC or a local IRB deems it necessary

If a mother withdraws consent prior to birth, the study intervention will not be performed and the mother's prenatal data and the reason for withdrawal of consent will be documented in the study database.

If maternal consent is withdrawn at any point after the study intervention, all data obtained prior to the time of consent withdrawal will be used for data analysis, but data will not be collected after withdrawal.

All participants that withdraw from the study will receive standard treatment.

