### **At Delivery**

#### **Initial Steps (both arms)**

- For **vaginal** deliveries, the infant will be placed on a stable surface near the introitus on a warming pad with OB towel and/or plastic drape to prevent hypothermia.
- For **Cesarean section** deliveries, the infant will be placed on the mother's pelvis or a suitable stable surface on a sterilely covered warming pad and sterile OB towel and/or sterile plastic drape.
- A heart rate monitor may be applied.
- The infant will be stimulated to breathe for up to 30 seconds from birth, including bulb suctioning of the mouth and nose if indicated.
- At 20 seconds from birth, the VFF will announce "20 seconds; Neo assess breathing. Is the baby breathing well or not?" The neonatology provider will assess breathing, and at 30 seconds announce "breathing well", or "not breathing well" and the VFF will record this.

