### **Subject Status Definitions**

Enrolled: A mother-infant dyad is considered “enrolled” in the study once the mother has signed the consent form.

Randomized: A mother-infant dyad is considered “randomized” at the time a study intervention assignment is allocated from the randomization module.

On-Study: A mother-infant dyad is considered “on-study” from the time of randomization, unless consent is withdrawn.

On Follow-up: A mother-infant dyad is considered “on follow-up” once the study intervention is completed.

Off-Study: The mother is considered “off study” at her discharge from the hospital after delivery. The infant is considered “off-study” once the infant reaches 36 weeks PMA, is discharged to home or dies, whichever comes first.

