### **Analysis Plan**

#### **Analysis Populations:**

##### **Intent-to-treat (ITT)**

The primary analysis will be based on all randomized eligible EPT infants, and will be based on the arm they were randomized to regardless of intervention received (intent-to-treat).

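### The withdrawal section lets a physician's decision against the intervention end study participation, contradicting the on-study definition and the intent-to-treat rule for randomized infants

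*Protocol*

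**What the plan says.** Protocol section 4, Discontinuation/Withdrawal from Study, opens: "Participants may be withdrawn or be discontinued from the study at any time for any of the following reasons". Four reasons follow: the mother's withdrawal of consent, closure of the study, a DSMC or IRB decision, and this one: "Obstetrician or neonatology physician determines that a maternal or fetal condition precludes the study intervention". All four stand on the same footing. Data rules are then given for withdrawn consent only; for withdrawal after the intervention, "If maternal consent is withdrawn at any point after the study intervention, all data obtained prior to the time of consent withdrawal will be used" and nothing further is collected. No data rule is attached to the physician's decision.

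Four other places bear on a dyad that has already been randomized:

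- Section 4, Subject Status Definitions: a dyad is on-study "from the time of randomization, unless consent is withdrawn". The same section starts the on-follow-up status only when the intervention has been completed.
- Section 4, the note under Mother (OB team): "In case of an unanticipated emergency, the Obstetrician or Neonatologist may terminate or deviate from the protocol".
- Section 7, Intent-to-treat (ITT): the primary analysis takes the randomized eligible infants and "will be based on the arm they were randomized to regardless of intervention received (intent-to-treat".
- Section 7, Handling protocol deviations or losses to follow-up: randomized on-study infants are assessed for endpoints despite major deviations or a later finding of ineligibility.

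**The concern.** A condition that rules out the intervention is a reason to withhold the intervention. It is not a reason to stop reading the infant's chart. The withdrawal section treats the two as one act, so a site could follow it to the letter and take a randomized infant out of the study, while the on-study definition and section 7 say that the infant stays in.

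The conflict matters because of when and by whom the ground would be used. Under Randomization (section 4) the assignment is displayed before delivery, and Rationale for Study Design (section 1) says that the intervention cannot be blinded. A decision made between randomization and birth is therefore made in knowledge of the arm, and for a medical reason likely to be linked to prognosis. If such decisions end follow-up, the infants lost may be at higher risk than those who stay, and the loss may differ between arms. Intent-to-treat analysis is meant to prevent exactly that.

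**Working it through.** **Step 1. The texts side by side, for a randomized dyad whose physician rules out the intervention**

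| Protocol section | Is the infant still in the study? |
|---|---|
| 4, Discontinuation/Withdrawal from Study | May be withdrawn from the study, at any time |
| 4, Subject Status Definitions, on-study | Yes, unless consent is withdrawn |
| 4, Subject Status Definitions, on follow-up | Unclear: starts on completion of an intervention that did not take place |
| 7, Handling protocol deviations | Yes, if on-study |
| 7, Intent-to-treat | Yes, in the assigned arm |

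The first row cannot be reconciled with the second. The fourth depends on on-study status, which is the point in dispute.

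**Step 2. The plan's own design figure**

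Inputs from section 7, Study Size Considerations: 172 infants per arm in cohort 1; gestational-age shares 0.38 and 0.62; Standard failure rates 0.551 and 0.256; odds ratio 0.5; two-sided 5%; uncorrected CMH test.

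- VentFirst failure at odds ratio 0.5: 0.380 and 0.147 in the two strata.
- With n per arm per stratum of 65.36 and 106.64 and weights h = n/2, the sum of h × difference is 32.68 × 0.1707 + 53.32 × 0.1092 = 11.40.
- Standard deviation of that sum: 4.09 under the null, 4.04 under the alternative.
- Power = Φ[(11.40 − 1.96 × 4.09)/4.04] = Φ(0.84), about 79.9%. The plan states about 80%, so the design figure reproduces.

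**Step 3. Loss unrelated to prognosis**

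The same formula, with only the VentFirst arm of cohort 1 reduced, gives 78.9% power at 5% loss and 77.7% at 10%. Lost numbers are a minor matter; selection is what counts.

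**Step 4. Loss related to prognosis (illustration)**

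Assume no true effect, failure rate 0.37 (the Standard proportion in Interim Analysis for Efficacy), and losses in VentFirst only. Let f be the fraction of VentFirst lost and r the failure rate among those lost. Both are assumptions. The lowest r used, 0.551, is the protocol's rate for the younger gestational stratum.

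Observed VentFirst failure: p = (0.37 − f·r)/(1 − f).

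Type I error, by a normal approximation without stratification: Φ[(d − 1.96·s0)/s1] + Φ[(−d − 1.96·s0)/s1]. Here d = 0.37 − p, and s0 and s1 are the pooled and unpooled standard errors with 172 and 172(1 − f) infants.

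Example, f = 0.05 (8.6 infants) and r = 0.9:

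- p = (0.37 − 0.045)/0.95 = 0.342, so d = 0.028.
- s0 = 0.0523 and s1 = 0.0523.
- Φ(−1.43) + Φ(−2.50) = 0.077 + 0.006 = 0.083.

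| f | r | Observed VentFirst failure | Apparent odds ratio | Two-sided type I error, cohort 1 |
|---|---|---|---|---|
| 2% | 55.1% / 70% / 90% | 36.6% / 36.3% / 35.9% | 0.98 / 0.97 / 0.95 | 5.1% / 5.2% / 5.5% |
| 5% | 55.1% / 70% / 90% | 36.0% / 35.3% / 34.2% | 0.96 / 0.93 / 0.89 | 5.4% / 6.3% / 8.3% |
| 10% | 55.1% / 70% / 90% | 35.0% / 33.3% / 31.1% | 0.92 / 0.85 / 0.77 | 6.6% / 10.6% / 20.1% |

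The shift favours VentFirst only because every loss was placed there. The same losses from Standard would reverse it, and equal losses at equal risk would cancel.

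**The case against.** The best reply is that the protocol already holds the right rule. The on-study definition admits only withdrawn consent, section 7 assesses on-study infants despite major deviations, and the analysis is intent-to-treat. This stands in part: it makes the fault an internal contradiction, not a settled instruction to drop infants. It does not remove the contradiction, because the section 7 rule covers on-study infants and the withdrawal section offers another way out of that status.

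Three further replies stand and narrow the point:

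- The withdrawal wording is permissive, and the only sentence that stops data collection concerns withdrawn consent. That a site would stop follow-up on a physician's decision is a possible use of the text, not something the text orders.
- Much of this ground will be used before randomization. Dyads are enrolled at consent, eligibility is rechecked before randomization, exclusion criterion 7 already covers physician concern, and randomization is preferably within an hour of delivery. A withdrawal before randomization loses no randomized infant.
- The emergency note speaks of terminating or deviating from the protocol, not of leaving the study, and Emergency Modifications (section 10) treats such departures as deviations or violations.

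A reader might also infer two stronger things.

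One is that the losses would fall mainly in VentFirst and so favour it. That is plausible, since Standard follows current recommendations, but the documents give no split. Standard also calls for at least 30 seconds before clamping, so an emergency can rule out either arm's procedure.

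The other is that infants without a breathing declaration drop out of both cohort analyses. The declaration ("The neonatology provider will assess breathing, and at 30 seconds announce") belongs to the initial steps of both arms. How an infant without one is classified is missing-data handling that a statistical analysis plan not at hand may settle. It is no part of this point.

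**Conclusion.** The point holds as a contradiction that should be removed. For randomized dyads, the physician ground in the withdrawal section cannot stand beside the on-study definition, the endpoint-assessment rule and the intent-to-treat rule. If it were used after randomization to end follow-up, it would allow arm-aware loss of infants likely to differ in prognosis.

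How much bias would follow, and in which direction, cannot be told from the documents. The 5.4% to 8.3% range for type I error in cohort 1 rests on an assumed 5% loss, all of it in VentFirst, and an assumed failure rate of 55% to 90% among those lost. At 2% loss the effect is negligible. The 20% figure needs the most extreme corner of the assumed grid and should not be read as an expected size. No stated sample size or power figure changes.

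**What to change.** Reword Discontinuation/Withdrawal from Study so that stopping the intervention and leaving the study are separate:

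- After randomization, a physician's decision that the intervention is precluded, or an emergency termination, ends only the intervention. The infant stays on-study in the assigned arm. Breathing status, the 7-10 day head ultrasound and outcomes to 36 weeks PMA are still collected.
- Data collection ends only if the mother withdraws consent, or if a DSMC, IRB or sponsor decision explicitly stops it.

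In Subject Status Definitions, define on follow-up so that it does not depend on completing the intervention. Neither change touches when clinicians may stop or depart from the intervention.

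The cost is a protocol wording change, chart abstraction for a few more infants, and a slight dilution of the effect by infants who did not receive the assigned intervention, which an intent-to-treat analysis accepts. According to section 6, outcomes come from routine care apart from the outside ultrasound readings, so little new work is created.

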### **Subject Status Definitions**

Enrolled: A mother-infant dyad is considered “enrolled” in the study once the mother has signed the consent form.

Randomized: A mother-infant dyad is considered “randomized” at the time a study intervention assignment is allocated from the randomization module.

On-Study: A mother-infant dyad is considered “on-study” from the time of randomization, unless consent is withdrawn.

On Follow-up: A mother-infant dyad is considered “on follow-up” once the study intervention is completed.

Off-Study: The mother is considered “off study” at her discharge from the hospital after delivery. The infant is considered “off-study” once the infant reaches 36 weeks PMA, is discharged to home or dies, whichever comes first.

## 5 EVALUATIONS AND ASSESSMENTS

### Time and Events Table

**Table 1: SCHEDULE OF EVENTS**

| Assessments / Procedures              | Pre-Study | Day 1 (Birth Day) | Follow-Up 1 st 24h | HUS at 7-10 days | Follow-Up 1 st 10 days | Final HUS 36 wks PMA +/- 7days | Follow-up 36 wks PMA  +/- 7 days | Follow-Up 18-24 months CGA |
|---------------------------------------|-----------|-------------------|-------------------------------|------------------|-----------------------------------|--------------------------------|----------------------------------------------|----------------------------|
| Review inclusion/exclusion criteria   | X         |                   |                               |                  |                                   |                                |                                              |                            |
| Obtain Informed Consent               | X         |                   |                               |                  |                                   |                                |                                              |                            |
| Medical history                       | X         |                   |                               |                  |                                   |                                |                                              |                            |
| Confirm eligibility       |           | X                 |                               |                  |                                   |                                |                                              |                            |
| Randomization                         |           | X                 |                               |                  |                                   |                                |                                              |                            |
| Vent First Study intervention         |           | X                 |                               |                  |                                   |                                |                                              |                            |
| Data collection + labs    |           | X                 | X                             |                  |                                   |                                | X                                            |                            |
| Head ultrasound (HUS)     |           |                   |                               | X                |                                   | X                              | X                                            |                            |
| Adverse events reporting  |           | X                 | X                             | X                | X                                 | X                              | X                                            |                            |
| Bayley III exam           |           |                   |                               |                  |                                   |                                |                                              | X                          |
| ASQ questionnaire         |           |                   |                               |                  |                                   |                                |                                              | X                          |
| MCHAT-R questionnaire     |           |                   |                               |                  |                                   |                                |                                              | X                          |
| General health assessment             |           |                   |                               |                  |                                   |                                |                                              | X                          |

1. Eligibility *must* be confirmed prior to study intervention. This is particularly important for mothers who have consented and are discharged and readmitted.
2. VentFirst delivery data collection will be done in real time in the delivery room. See the Vent First delivery forms. See other CRF's for all other follow-up data collection required.
3. A window of up to 14 days post birth is allowed to repeat the day 7-10 HUS if the original scan was judged to be inadequate by site radiology attending.
4. See Section 8 for description of expedited vs routine reporting requirements.
5. If an infant is discharged to another facility prior to 36 wks PMA final follow-up, a member of the study team will obtain maternal consent and then will contact the outside facility to obtain status at 36 weeks PMA.
6. Bayley III exam, ASQ and MCHAT are standard neurodevelopmental tests routinely performed on preterm infants at 18-24 months CGA. .

### Pre-Study Intervention Assessments

There are no study-specific assessments required prior to the VentFirst intervention. All procedures, assessments, and laboratory tests prior to delivery are those that would be done as part of routine care.

### Study Assessments

There are no specific on-study assessments required for this protocol other than that the mother-infant dyad must meet all eligibility criteria prior to consent *and* prior to randomization.

### **Follow-up Assessments**

After the delivery room intervention, infants are followed for clinical outcomes and adverse events until 36 weeks PMA or until death or discharge home, whichever comes first. A 36 week PMA chart review follow-up will be done by a member of the study team. If the infant has been transferred to an outside facility prior to 36 weeks PMA a study team member will obtain maternal consent and follow-up with the outside facility to collect the relevant study data. At 18 – 24 months CGA infants will return for a Neurodevelopmental follow-up clinic visit that is part of routine care. Neurodevelopmental follow-up data, such as results from Bayley III testing, ASQ and MCHAT-R questionnaires and general health data will be collected for study purposes. General health information can include data such as: current medications, issues with chronic lung disease, seizures, and surgeries or hospitalizations after NICU discharge.

